**Methods:**

Thirty adults aged 18 to 70 years diagnosed with an anxiety disorder will be recruited for this study. Participants will be randomised into an intervention group (high-intensity training) and a control group (low-intensity training). Randomisation will be performed using counterbalanced block randomisation in a 1:1 ratio, stratified by sex. Both groups will perform 4 weeks of twice-weekly training supervised by an exercise physiologist. The primary outcome will be the total score on the Hospital Anxiety and Depression Scale (HADS) and the total score on the Beck Anxiety Inventory (BAI). The secondary outcomes include blood-pressure changes and adherence. Evaluations will be performed at baseline and following 4 weeks of the interventions, and 6 months after the termination of the intervention period (secondary endpoint).

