## Methods/design

This is a study protocol for a randomised controlled trial designed to test the effects of high intensity training compared to low intensity training on anxiety levels.

There will be a random 1:1 allocation into two groups. The two groups are high intensity exercise (1 × 4 minutes performed two times per week with a heart rate of 85–95% of maximal heart rate, corresponding to ≥ 16 on the 6–20 Borg scale) and low intensity exercise (45 minutes performed two times per week with a heart rate of approximately 60% of maximal heart rate, corresponding to 9–11 on the 6–20 Borg scale) [26]. The high intensity group will perform a 10-minute warm-up prior to the high-intensity bout, and a 5-minute cooldown. Due to the low intensity in the low intensity group, a warm-up is not considered necessary.

The total amount of training sessions for both groups will be eight. The high intensity exercise group will serve as the intervention group, while the low intensity exercise group will serve as an active control group.

The trial will be conducted in accordance with the Standard Protocol Items: Recommendations for Interventional Trials statement (SPIRIT) [27].

The trial has been approved by the Data Protection Officer at the University Hospital of North Norway and the Regional Committee on Health Research Ethics (approval number 714458) and registered at ClinicalTrials.gov (Trial registration number NCT06881758).

Participants will provide written informed consent before allocation to the two intervention groups, and they will be randomised into a high-intensity training group and a low-intensity training group, following baseline measures.

Randomisation will be performed using counterbalanced block randomisation in a 1:1 ratio, stratified by sex, to ensure an equal distribution of males and females across the study groups. Block sizes of four–six participants will be used. This will allow for a balanced representation of both genders in each condition. Randomisation will be conducted using a computer-generated random number sequence via the website https://www.randomizer.org/.

Outcomes will be measured immediately after inclusion (baseline), right after the very last exercise session, four weeks after the last exercise session (primary endpoint) and three months after the termination of the intervention period (secondary endpoint) (Fig. 1).

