**ASSESSMENTS:**					
***Demograpichs***	X	X			
***MINI***		X			
***BAI***		X	X	X	X
***HADS***		X	X	X	X
***Blood pressure***		X	X	X	X
***EKG***		X	X	X	X

*MINI* Mini International Neuropsychiatric Interview [28], *BAI* Beck Anxiety Inventory [24], *HADS* Hospital Anxiety and Depression Scale [25], *EKG* electrocardiogram

t_1_ = right after the very last exercise session

t_2_ = four weeks after the last exercise session

t_3_ = three months after the termination of the intervention period

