## Outcomes

### Primary outcome measures

The primary outcome measure will be the degree of anxiety symptoms measured by the Hospital Anxiety and Depression Scale (HADS) [25] and the Beck Anxiety Inventory (BAI) [24] prior to the first (pre) and after the last (post) training session is completed.

The HADS is a questionnaire that measures self-report levels of some symptoms of anxiety and depression [25]. The instrument consists of 14 questions (items), of which 7 are related to anxiety symptoms (HADS-A) and 7 to depression symptoms (HADS-D). Each item is rated from 0 to 3, which gives a range of scoring from 0 to 42, with a score ranging between 0 and 21 for the anxiety (HADS-A) and depression (HADS-D) subscales. The HADS is one of the most commonly used self-report instruments for measuring anxiety and depression [29] and has demonstrated good reliability and validity and has sound psychometric properties [29]. A previous study found a minimal clinically important difference (MCID) between 0.5 and 5.57 for the HADS-D, and between 0.81 and 5.21 for HADS-A [30]. We will calculate total HADS scores and subscores for anxiety symptoms and depressive symptoms, respectively.

The Beck Anxiety Inventory (BAI) [24] is a questionnaire that measures self-report levels of some symptoms of anxiety. The instrument consists of 21 questions (items), and each item is rated from 0 to 3, which gives a range of scoring from 0 to 63, a higher score indicating increased symptoms. The BAI measures anxiety symptoms including muscle tension, dizziness, racing heart, nervousness, fear of dying, abdominal discomfort, face flushing, sweating, light-headedness, fear of the worst happening and a feeling of choking. The BAI is one of the most commonly used self-report instruments for measuring anxiety [31] and has demonstrated good reliability and validity and has sound psychometric properties [32]. We will calculate total BAI scores.

Both the Hospital Anxiety and Depression Scale (HADS) and the Beck Anxiety Inventory (BAI) will be applied. HADS allows comparability with both psychiatric and somatic populations, while BAI provides a more detailed assessment of somatic anxiety symptoms. Using both HADS and BAI increases sensitivity and also validity in assessing anxiety.

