### Statistical analysis

Data management and analyses are performed using SPSS 30 (SPSS Inc., Chicago, IL, USA). Data will be analysed using descriptive and inferential statistics. Continuous variables are presented with mean ± SD and 95% CIs.

The effect of the intervention will be assessed by examining change scores on the BAI and HADS (primary outcomes) and blood pressure and EKG (secondary outcomes). Changes from baseline to post-tests (immediately, after four weeks, and after three months) will be analysed.

Single measures (e.g. baseline data) will be analysed using ANOVA or linear regression, provided the statistical assumptions for linear models are met. Variables will be assessed for normality through visual inspection of histograms and Q-Q plots, along with a formal test for normality (Shapiro-Wilk test). If the assumption of normality is violated, non-parametric tests will be applied. ANOVA with repeated measures will be used to analyse changes in quantitative data (change scores) and to compare the two groups.

Missing data will be handled using linear mixed-model analyses, which provide unbiased estimates under the assumption that data are missing at random and allow inclusion of all available observations. Furthermore, multiple imputation will be applied as a sensitivity analysis to assess the robustness of the results to potential missingness.

We will also use Bonferroni corrected post hoc comparisons when performing multiple comparisons, ensuring that the overall significance level remains accurate. Additionally, effect sizes are estimated based on Cohen’s *d* (0.2 = small effect, 0.5 = medium effect, and 0.8 = large effect).

Participants with mild-to-moderate depressive symptoms will be eligible for inclusion, as anxiety and depression frequently co-occur in clinical populations. Due to our limited sample size, formal subgroup analyses based on depression status will not be conducted. Instead, the baseline depressive symptom scores (HADS-D) will be entered as a covariate in the statistical models to adjust for their potential influence on anxiety outcomes.

Age will be included as a covariate in all primary and secondary analyses. In addition, exploratory subgroup analyses will be performed by age group (< 40 years vs ≥ 40 years).

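### The Methods and the Outcomes section place the primary endpoint at different visits, so on this text the visit that decides the trial is not fixed

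*Protocol article*

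**What the plan says.** Four places in the protocol article bear on the timing of the primary endpoint.

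- **Methods/design** lists baseline, a visit directly after the final session, and then "four weeks after the last exercise session (primary endpoint) and three months after the termination of the intervention period (secondary endpoint". The visit directly after the final session carries no label.
- **Primary outcome measures** defines the primary outcome as anxiety symptoms on the HADS and BAI "prior to the first (pre) and after the last (post) training session is completed".
- **Abstract, Methods** states: "Evaluations will be performed at baseline and following 4 weeks of the interventions, and 6 months after the termination of the intervention period (secondary endpoint". It labels no visit as primary and does not mention a visit four weeks after training.
- **Table 1** treats the visits as distinct: t1 is "right after the very last exercise session", t2 is "four weeks after the last exercise session" and t3 is "three months after the termination of the intervention period". BAI and HADS are collected at all three.

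Two further sections are silent on which visit is primary. The Statistical analysis section says "Changes from baseline to post-tests (immediately, after four weeks, and after three months) will be analysed". The Sample size calculation uses post-treatment BAI means of 14 and 22 without naming a visit.

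**The concern.** The visits t1 and t2 answer different questions. At t1 the arms are compared at the end of supervised training. At t2 they are compared after four weeks without scheduled sessions. The article itself says its schedule is meant to capture both short-term and residual effects, so it does not treat the two as interchangeable.

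An analyst following Methods/design would run the primary comparison at t2. One following the Outcomes section would run it at t1. Two things are at stake. The first is control of the false-positive rate, if the choice between visits is made once results are visible. The second is whether the effect assumed in the sample size belongs to the visit finally used.

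**Working it through.** **1. The passages side by side**

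| Section | Visit it points to | Calls it primary? |
|---|---|---|
| Methods/design | t2 | Yes, by label |
| Primary outcome measures | t1 (before first to after last session) | Yes, by defining the primary outcome |
| Abstract, Methods | t1 (after the 4-week intervention); t2 absent | No |
| Table 1 | t1, t2, t3 as separate visits | No |
| Statistical analysis | all three post-tests | No |
| Sample size calculation | post-treatment, visit not given | No |

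The first two rows contradict each other. The abstract is weaker support for t1. The last three rows neither conflict with the others nor settle the matter.

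**2. The plan's own sample size**

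Inputs from the Sample size calculation: difference 22 − 14 = 8, SD 7, two-sided alpha 0.05, power 80%, attrition 20%.

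n per arm = 2 × [SD × (z₀.₉₇₅ + z₀.₈₀) / difference]² = 2 × [7 × (1.960 + 0.842) / 8]² = 12.02

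This agrees with the stated 12 per arm (24 in total), apart from rounding 12.02 down. Inflation gives 24 / (1 − 0.20) = 30, as stated. An exact t-test with 12 per arm has power of 76%. These figures hold at whichever visit the 8-point difference applies to, and the article does not say which that is.

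**3. Type I error with a free choice of t1 or t2**

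One scale, each visit tested at two-sided 0.05. If the two tests were independent: 1 − 0.95² = 9.75%.

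Repeated measures are correlated, and the article gives no correlation, so a range is assumed. Null trials were simulated with normal outcomes, 12 per arm and a two-sample t-test at each visit, and a trial was counted as positive if either test was significant:

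| Assumed between-visit correlation | Type I error |
|---|---|
| 0.5 | 9.0% |
| 0.7 | 8.4% |
| 0.9 | 7.2% |

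**4. Power if the difference is smaller at the chosen visit**

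Exact t-test, SD 7, 12 per arm. All differences other than 8 are assumptions:

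| Difference (BAI points) | Power |
|---|---|
| 8 | 76% |
| 6 | 52% |
| 5 | 39% |
| 4 | 27% |

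**The case against.** **After the last session could include t2.** Read loosely, it could. But the pre/post wording and the abstract point to the end of training, and a reading wide enough to include t2 would include t3 as well and so fix nothing.

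**A Bonferroni correction is planned.** The Statistical analysis section commits to it for post hoc comparisons, without stating the family of tests. If it covered the two visits (each tested at 0.025), the type I error would be about 4.3% at correlation 0.7. That would control the error rate, but it would still not say which visit is primary.

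**The registry entry or the full protocol may name the visit.** This stands in part. Neither is available here, and the article says that protocol and registration together carry the required registration items. The conclusion is therefore limited to this text. It concerns two statements that conflict, not a detail left out.

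**Stronger readings that the document does not support.**

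- A reader might count three visits and two scales and conclude that the false-positive rate is near 19%. But t3 is labelled secondary wherever the text ranks it, and having two primary scales is a separate multiplicity question.
- A reader might take the 3-month versus 6-month discrepancy as further doubt about the deciding visit. It concerns only the secondary endpoint, and six months appears only in the abstract.
- A reader might count the sample size and analysis sections as further contradictions. They are silent on the primary visit, which is not the same thing.
- A reader might infer that t2 must be right because it alone carries the label. The Outcomes section and the abstract point the other way, and the text does not establish that the 8-point difference applies at t2.

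**Conclusion.** The contradiction is real and should be resolved before analysis, because it concerns the trial's deciding comparison. It lies between Methods/design (t2) and the primary outcome definition (t1), with the abstract lending some support to t1. On this text alone the primary visit is open. The illustrative cost is a type I error of about 7% to 9% instead of 5% for one scale. That figure assumes 12 per arm, an unadjusted choice between t1 and t2 after the results are seen, and a between-visit correlation of 0.9 to 0.5. It measures the freedom the wording leaves and is no forecast of what the investigators will do.

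The stated sample size of 24, inflated to 30, is not put in doubt by this point, except that the visit to which the 8-point difference belongs is not named. The secondary-endpoint discrepancy is minor.

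**What to change.** Before any by-arm data are examined:

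1. Name one primary visit, t1 or t2, and make the other visits secondary.
2. Use the same wording in the abstract, Methods/design, Primary outcome measures, Statistical analysis and Table 1.
3. State in the Sample size calculation that the assumed 8-point BAI difference applies at that visit. If a smaller difference is expected there, restate the power.
4. Check that the registry entry agrees.
5. Reconcile the abstract's 6-month secondary endpoint with Methods/design, Table 1 and Statistical analysis, which put the last visit at three months. No 6-month visit is scheduled.

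The cost is protocol wording and, if needed, a registry update. Both candidate visits already collect BAI and HADS, so no visit is added. Extra participants would come into question only if the restated power at the chosen visit proved inadequate.

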**Fig. 1 Fig1:**
[figure not shown]
Study procedure flow chart

This approach allows for the assessment of the short-term effects of intervention and any residual effects.

Before the baseline measures, the participants are familiarised with the experimental procedures and devices used.

Table 1 is a SPIRIT diagram for trial stages of enrolment, intervention and assessment.

**Table 1 Tab1:** SPIRIT diagram for trial stages of enrolment, intervention and assessment

	**STUDY PERIOD**				
	**Enrolment**		**Post-allocation**		
**TIMEPOINT****	***Pre –enrolement***	**Baseline**	***t***_***1***_	***t***_***2***_	***t***_***3***_
**ENROLMENT:**					
**Eligibility screen**	X				
**Written informed consent**		X			
***Randomization***	X				
**ASSESSMENTS:**					
***Demograpichs***	X	X			
***MINI***		X			
***BAI***		X	X	X	X
***HADS***		X	X	X	X
***Blood pressure***		X	X	X	X
***EKG***		X	X	X	X

*MINI* Mini International Neuropsychiatric Interview [28], *BAI* Beck Anxiety Inventory [24], *HADS* Hospital Anxiety and Depression Scale [25], *EKG* electrocardiogram

t_1_ = right after the very last exercise session

t_2_ = four weeks after the last exercise session

t_3_ = three months after the termination of the intervention period

## Study setting

The study will take place at the Division of Substance Use and Mental Health at the University Hospital of North Norway, UNN-Åsgård, [name], Norway.

The study participants will be examined by medical staff (doctors) to assess eligibility for participation in the study. The screening will include a clinical interview where the MINI-interview will be used [28]. The following descriptive characteristics will be collected: sex, age, body weight, height, waist circumference, blood pressure, pulse, respiratory frequency, temperature, somatic and psychiatric diagnoses and current medication.

Furthermore, a medical examination will be performed in order to ensure the patient can handle the physical training. In addition, a resting state EKG will be taken, a blood sample will be drawn, and the following analyses will be performed: haemoglobin, haematocrit, HbA1c, electrolytes, liver function tests, kidney function tests, TSH and fT4, lipids and PRO-BNP.

Following inclusion in the study, a study nurse will assist the participants in performing the psychometric tests.

At the study Hospital, there are two separate rooms for physical training, fitted with treadmills and other equipment for physical training. The interventions (physical training) will be carried out with the supervision of an exercise physiologist.

The treadmills are of the type Lexco T560 (Lexco, South Korea) and the patients will also be fitted with heart monitor belts of the type Polar H10 (Polar Electro, Finland).

## Trial coordination and oversight

The trial is coordinated by the Division of Mental Health and Substance Use at the University Hospital of North Norway, which also serves as the sponsor institution. The principal investigator ([name]) has overall responsibility for the scientific and ethical conduct of the study, including recruitment, data integrity and adherence to the approved protocol.

Coordination and follow-up of study activities are handled by the study coordinator ([name]), who oversees scheduling, data collection and communication among study staff. The principal investigator and study coordinator meet regularly to review study progress, recruitment and safety issues. Given the limited scope and low-risk nature of this single-site trial, no formal Trial Steering Committee or independent monitoring group has been established. Oversight is provided by the sponsor and the Regional Committee for Medical and Health Research Ethics (REK North) in line with applicable Norwegian regulations.

## Trial oversight and quality assurance

As this is a small-scale, single-site clinical study involving a low-risk behavioural intervention, no formal Data Monitoring Committee or external auditing procedures are established.

Oversight of the study is carried out by the authors who are responsible for monitoring recruitment progress, data quality and adherence to the approved protocol. They will hold regular internal meetings to review study progress and ensure that the study follows ethical and institutional guidelines.

Any protocol deviations or adverse events will be reported to the Regional Committee for Medical and Health Research Ethics (REK North).

## Participants

### Inclusion criteria

Eligible participants are patients aged 18–70 years, with anxiety disorders in accordance with ICD-10 criteria, including (but not limited to) generalised anxiety disorder, agoraphobia, panic disorder, social phobia, post-traumatic stress disorder, hypochondria and obsessive–compulsive disorder. Comorbidity will often occur, so the patient may also have symptoms of depression. However, the main disorder should be anxiety.

### Exclusion criteria

The exclusion criteria are somatic diseases that may impede training or where training may have a detrimental effect, for instance severe cardiovascular disease, severe asthma, severe COPD, cancer and poorly regulated diabetes. People with severe mental disorders such as schizophrenia or bipolar disease, and people with an increased risk of suicide, and those with substance addiction, will not be eligible for inclusion. People using anxiolytics (benzodiazepines) and sleeping medication (z-hypnotics, melatonin, antihistamines) can be included provided this medication is used infrequently and in small doses.

### Intervention group

The intervention comprises 4 weeks of high-intensity exercise. Two training sessions will be completed each week, with a total of 8 sessions during the intervention period. Each session will include running or walking (depending on the participant’s level of fitness) on the treadmill for 4 minutes at a high level of intensity. The intensity is measured by the participant’s heart rate, which should be above 85% of maximal heart rate, and a rating of perceived exertion using the Borg scale of ≥ 16. To ensure sufficient intensity, the treadmill will be set at a minimum of 5%, similar to previous studies on interval training [17].

Participants will otherwise be encouraged to maintain their daily routine but refrain from changing their current pharmacological treatment or initiating other physical exercise practices during the study.

The high intensity exercise group will serve as the intervention group, while the low intensity exercise group will serve as an active control group.

### Comparison group

The comparison group comprises 4 weeks of low-intensity exercise. Two training sessions will be completed each week, with a total of 8 sessions during the intervention period. Each session will include running or walking (depending on the participant’s level of fitness) on the treadmill for 45 minutes at a low level of intensity. The intensity is measured by the participant’s heart rate, which should be approximately 60% of maximal heart rate, and a rating of perceived exertion using the Borg scale of 9–11.

Participants will otherwise be encouraged to maintain their daily routine but refrain from changing their current pharmacological treatment or initiating other physical exercise practices during the study.

## Outcomes

### Primary outcome measures

The primary outcome measure will be the degree of anxiety symptoms measured by the Hospital Anxiety and Depression Scale (HADS) [25] and the Beck Anxiety Inventory (BAI) [24] prior to the first (pre) and after the last (post) training session is completed.

The HADS is a questionnaire that measures self-report levels of some symptoms of anxiety and depression [25]. The instrument consists of 14 questions (items), of which 7 are related to anxiety symptoms (HADS-A) and 7 to depression symptoms (HADS-D). Each item is rated from 0 to 3, which gives a range of scoring from 0 to 42, with a score ranging between 0 and 21 for the anxiety (HADS-A) and depression (HADS-D) subscales. The HADS is one of the most commonly used self-report instruments for measuring anxiety and depression [29] and has demonstrated good reliability and validity and has sound psychometric properties [29]. A previous study found a minimal clinically important difference (MCID) between 0.5 and 5.57 for the HADS-D, and between 0.81 and 5.21 for HADS-A [30]. We will calculate total HADS scores and subscores for anxiety symptoms and depressive symptoms, respectively.

The Beck Anxiety Inventory (BAI) [24] is a questionnaire that measures self-report levels of some symptoms of anxiety. The instrument consists of 21 questions (items), and each item is rated from 0 to 3, which gives a range of scoring from 0 to 63, a higher score indicating increased symptoms. The BAI measures anxiety symptoms including muscle tension, dizziness, racing heart, nervousness, fear of dying, abdominal discomfort, face flushing, sweating, light-headedness, fear of the worst happening and a feeling of choking. The BAI is one of the most commonly used self-report instruments for measuring anxiety [31] and has demonstrated good reliability and validity and has sound psychometric properties [32]. We will calculate total BAI scores.

Both the Hospital Anxiety and Depression Scale (HADS) and the Beck Anxiety Inventory (BAI) will be applied. HADS allows comparability with both psychiatric and somatic populations, while BAI provides a more detailed assessment of somatic anxiety symptoms. Using both HADS and BAI increases sensitivity and also validity in assessing anxiety.

